**Fig. 2 Fig2:**
[figure not shown]
Flow diagram of the clinical trial

The primary outcomes will be measured by two tests. The walking distance measured with a standardized treadmill test [34, 35] is a widely used tool for functional assessment and monitoring of exercise rehabilitation, where PFWD, FWD, and MWD are objective measures of improvement. In turn, the 6MWT is an individualized test that assesses the submaximal level of functional capacity [35, 38]. The patient chooses the intensity of the exercise and can rest during the test, which better reflects the functional level of exercise practiced in daily physical activities. Therefore, we chose to use both measures (walking distance measured with the treadmill test and walking distance measured with the 6MWT) not only because they complement each other but also because both provide different and valuable information.

The primary outcomes will reflect the effectiveness (beneficial effect) and not the harm (adverse effect) of the intervention. The change achieved in primary outcomes from baseline to 3 and 6 months will be a valid, reproducible, and relevant result for the target population and healthcare professionals. The amount of change achieved will be represented in a continuous variable that will facilitate comparisons and grouping of results across studies, trials, and meta-analyses. Data collection forms can be requested from the responsible investigator.

### Plans to promote participant retention and complete follow-up {18b}

The implementation of strategies to promote adherence and prevent dropout is one of the most important aspects in trials, especially when the few studies reporting dropout rates, have dropout rates ranging from 12 to 27.5% [15–17]. Thus, to minimize attrition and promote adherence, the following strategies will be used: (1) during the invitation phone call, the physician will explain the objectives, benefits, and importance of participating in the study; (2) participants who agree to participate in the study will be offered a Diploma of Commitment where participation is presented as something positive and not accessible to everyone (Congratulations! You have been selected to participate in this study!). The diploma informs that the participant becomes part of a group of people who will undergo physical exercise treatment for PAD, the start and end dates of treatment and study, and the dates of face-to-face sessions at the hospital for evaluations formalities over the 6 months. (3) In these evaluations, a medal will be offered (pin format) and a report with individualized and systematized information on the results obtained with regard to the main result; (4) reminder messages will be sent whenever the date of the formal hospital assessment approaches; (5) congratulatory messages will be sent on each participant’s birthday, as well as congratulatory messages for being part of the study each month; (6) a Facebook page will be created to share information about the disease and the importance of physical exercise, and (7) a 24-h telephone number will be provided to support participants in the event of adverse events. Participants who discontinue or deviate from intervention protocols will be invited to attend the assessments in order to implement an intention-to-treat data analysis protocol at the end of the study.

### Data management {19}

Data will be entered as it is collected. The data collection forms—a set of questionnaires and the respective quotation for each item and total instrument score—will be transferred to the SPSS database. A member of the research team will enter the data and each time the database is closed will do a descriptive analysis of the data to ensure that the range of data values is correct in each variable. The data collection forms used, and their quotation will be available upon request from the principal investigator. Data will be analyzed by a data analyst who will be blinded to participant allocation. Questionnaires will be destroyed once the data is published.

### Confidentiality {27}

The procedures for storing, processing, and protecting personal data will respect the current General Data Protection Regulation (Regulation (EU) 2016/679), Portuguese Law No. 58/2019 of 8 August. Each participant will be assigned a code (unique identification number) in several databases to ensure data independence. All information about the practice of physical exercise obtained through the mobile app will be stored in an online data system platform. The WalkingPad web platform is accessible to team members and patients. As long as the patient remains in the clinical trial, he accepts that the entire research team has access to the data recorded by the WalkingPad web platform. As for the assessment data, only the principal investigator and the data analyst will have access to the complete dataset, which will be stored in different locations and used for research purposes only. Passwords will be used to ensure the protection and security of data (and participants).

### Plans for collection, laboratory evaluation, and storage of biological specimens for genetic or molecular analysis in this trial/future use {33}

This trial does not involve collecting biological specimens for storage.

## Statistical methods

### Statistical methods for primary and secondary outcomes {20a}

The first step in the data analysis plan will be the screening of data to detect errors and missing values, although missing data is not expected in the questionnaires, as the data collection will be carried out in person with a researcher who will guarantee its complete completion. Missing values may be present when a participant withdraw or refuse to participate in the assessment, or missing values in physical tests due to physical limitations or difficulties in performing physical performance tests (e.g., treadmill test). Second, a summary of baseline sociodemographic, clinical, physical, and psychological variables will be provided through descriptive statistics. Third, comparisons will be made between the three groups to examine whether there are differences between the groups at baseline in all variables. As the sample was stratified, differences in fundamental variables such as age and maximal walking distance are not expected to be found. In addition, differences at baseline between participants who will complete the study and those who drop out will be examined. Fourth, primary outcome analyses will be conducted on an intention-to-treat basis, including all participants analyzed as randomized. The primary outcome will be analyzed using multiple regressions with adjustment for MWD, PFWD, and FWD. A mixed ANOVA will be performed to test the mean differences between the three groups (between-subject factor) and over the three measurement points (in-subject factor). Results will be reported as the difference in MWD, PFWD, and FWD from t1 to t2, t2 to t3, and t1 to t3, as well as the mean differences between GE1 and GE2, and ACG with 95% confidence intervals. To determine the minimal clinically important difference (MCID), a change in scores for the primary outcome will be calculated by subtracting the baseline outcome from the t2 (3 months) and t3 (6 months) outcomes for each participant. The least important difference (MID) for improvement and deterioration will be defined by the upper and lower limits of the 95% confidence interval of the mean change in MWD, PFWD, and FWD [71]. Twenty meters was defined as MCID [17]. However, a recent meta-analysis [19] showed significant heterogeneity in the magnitude of effect estimates for MWD (*χ*^2^ = 16.4, *p* = 0.022) and PFWD (*χ*^2^ = 19.6, *p* = 0.003). The mean change (SD) in MWD for patients randomly allocated to home exercise or programs with no exercise plan ranges from 24 (166) to 402 (391) m and PFWD changes range from 21 (81) to 182 (249) m.

Finally, secondary outcomes (walking ability and general and specific health-related QoL) will be similarly analyzed. Mediation and moderation analyses will be performed to examine mechanisms of influence (process variables) as well as Structural Equation Modeling (SEM) that will allow the analyses of complex relationships between variables and test causal relationships explaining initial behavioral change throughout time. Measures of effect size and statistical power (1−*β*) will be presented for all statistical tests performed. All planned tests are two-tailed. Statistical significance will be set at *P* ≤ 0.05. IBM® SPSS® V.26 and IBM® IPSS® Amos™ will be used to perform all data analyses.

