**Methods:**

This is a single-center, prospective, three-arm, single-blind, randomized, controlled, superior clinical trial with stratified and blocked random allocation. Three hundred participants with PAD and IC will be recruited from an Angiology and Vascular Surgery Department, Centro Hospitalar Universitário Porto (CHUPorto), Porto, Portugal. All patients will receive the same medical care recommended by  current guidelines. Participants in all three groups will receive a personalized prescription for an HBET program and a behavioral change and motivational intervention. Participants in experimental groups 1 and 2 will receive a smartphone with the WalkingPad app to monitor exercise sessions. Experimental group 2 WalkingPad app will have a built-in virtual assistant that will promote behavioral change and provide motivational support. Participants allocated to the active control group will not receive the m-health tool, but a practice diary to encourage monitoring. The  program will last for 6 months with three evaluation moments (baseline, 3, and 6 months). The primary outcome will be the change in distances walked (maximal and pain-free) from baseline to 3 and 6 months. Secondary outcomes will be changes in quality of life, patients’ perception of resistance, and walking speed.

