### Sample size {14}

The sample size was calculated for an effect size of 0.25, a statistical power of 80%, and a significance level of 5%; á priori 57 participants will be needed in each of the groups (G*Power software, version 3.1.9). This calculus was based on previous studies (*F* tests, ANOVA: repeated measures, within-between interaction) [15, 17]. The calculated sample size is expected to be reached by the end of May 2022.

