## Assignment of interventions: allocation

### Sequence generation {16a}

After the identification of patients through consultation of the outpatient database, the fulfillment of the inclusion criteria in the screening session and the patient’s agreement to participate in the study, a random sequence will be created using a random number allocation software, by a researcher external to the team involved in the execution of this study, in order to guarantee the concealment of the allocation of participants by the different groups. Randomization will be carried out in blocks with four strata and the eligible participants will be randomly assigned to three groups, in blocks of multiples of five, and will be stratified according to (i) age (50 to 65 years old; 66 to 80 years old) and (ii) MWD at the baseline (50 to 275 m; 276 to 500 m). The entire process will be overseen by a researcher who will not be directly involved in the intervention or assessments. This researcher will inform the research team of the final allocation of each participant.

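### Two analyses are named for the primary walking distances without saying which decides, and the mixed ANOVA is described without the group-by-time interaction on which the trial was sized

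*Protocol article*

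**What the plan says.** In the Protocol article, Statistical methods for primary and secondary outcomes {20a}, two consecutive sentences cover the primary analysis. The first reads: "The primary outcome will be analyzed using multiple regressions with adjustment for MWD, PFWD, and FWD". It gives no dependent variable or time point, and does not say that the adjusting distances are baseline values. The second reads: "A mixed ANOVA will be performed to test the mean differences between the three groups (between-subject factor) and over the three measurement points". Neither analysis is called primary, deciding or supportive. The section then plans to report the changes t1 to t2, t2 to t3 and t1 to t3, with differences between arms and 95% confidence intervals, and marks none of them as decisive. Secondary outcomes are to be handled in the same way.

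Sample size {14} rests on a different description: "ANOVA: repeated measures, within-between interaction", with the result that "57 participants will be needed in each of the groups". Plans for assessment and collection of outcomes {18a} treats the endpoint as change: "The change achieved in primary outcomes from baseline to 3 and 6 months".

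**The concern.** A regression coefficient for arm, a group-by-time interaction and a group main effect answer different questions and need not agree on the same data. If the plan does not say which one decides, the choice can be made after the results are seen, and the false-positive rate for a single distance rises above 5%. This is separate from the number of distances or arm pairs tested: it arises for one distance alone.

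The description of the ANOVA adds to the uncertainty. An effect on change from baseline shows up in the group-by-time interaction. {20a} lists the group factor and the time factor and stops there. The time effect compares no arms, and all three arms receive a walking prescription. The group effect averages t1, t2 and t3, so it includes a visit at which no intervention effect can exist. Anyone who took it as the answer would be testing a diluted contrast.

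**Working it through.** **1. The plan's own figure.** Inputs from {14}: effect size 0.25 (read as Cohen's f), power 80%, alpha 5%, k = 3 groups, m = 3 visits. The between-visit correlation rho is not stated. For the interaction under sphericity, lambda = f²·N·m/(1 − rho) with (k − 1)(m − 1) and (N − k)(m − 1) df.
- rho = 0.5: N = 36 gives lambda = 0.0625 × 36 × 3 / 0.5 = 13.5 and power 82%, so 12 per group.
- rho = 0: 23 per group.
- SPSS-type and Cohen-type effect-size options: 34 and 33 per group.
- Group main effect, rho = 0.5, lambda = f²·N·m/(1 + 2·rho): 36 per group.
- One-way ANOVA: 53 per group.

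None of these gives 57 per group. That is a separate matter. What counts here is that the same f leads to very different sample sizes depending on which test decides.

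**2. Dilution in the group main effect.** If one arm differs by D at 3 and 6 months, its three-visit mean differs by (0 + D + D)/3 = 2D/3. If the difference grows linearly to D at 6 months, it is (0 + D/2 + D)/3 = D/2. Neither result depends on rho.

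**3. Power of the three candidates.** Assumptions: one arm better by D = 0.5 SD at both follow-ups, the other two arms equal, unit SD, equal correlation rho between visits, no dropout, n per arm. The factor 2/3 comes from one of three arms being shifted.
- Group main effect: lambda = n·(2/3)·(2D/3)² / [(1 + 2·rho)/3]
- Interaction: lambda = n·(2/3)·(2D²/3) / (1 − rho)
- Baseline-adjusted 6-month comparison: lambda = n·(2/3)·D² / (1 − rho²)

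For n = 57 and rho = 0.5:
- Group main effect: 38 × 0.111 / 0.667 = 6.33 on 2 and 168 df, power 60%.
- Interaction: 38 × 0.167 / 0.5 = 12.67 on 4 and 336 df, power 82%.
- Baseline-adjusted comparison: 38 × 0.25 / 0.75 = 12.67 on 2 and 167 df, power 90%.

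| n per arm | rho | Group main effect | Interaction | Baseline-adjusted, 6 months |
|---|---|---|---|---|
| 57 | 0.3 | 70% | 66% | 83% |
| 57 | 0.5 | 60% | 82% | 90% |
| 57 | 0.7 | 52% | 97% | 98% |
| 57 | 0.8 | 49% | 99.8% | 99.7% |
| 100 | 0.3 | 92% | 91% | 98% |
| 100 | 0.5 | 85% | 98% | 99% |

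The 100 per arm is the recruitment target of 300 divided by three. The allocation ratio is not stated and is taken as equal. With linear growth to 0.5 SD (n = 57, rho = 0.5) the three powers are 37%, 68% and 90%.

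**4. False positives from an open choice.** Simulation with no arm effect, one distance, each test at 0.05, 57 and 100 per arm:
- interaction or regression significant: about 7 to 9%;
- interaction, regression or group main effect significant: 11 to 13%.

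**5. How often the two main candidates differ.** With a sustained difference of 0.4 SD, exactly one of interaction and regression is significant in 28%, 14% and 5% of trials at rho 0.5, 0.7 and 0.8 with 57 per arm. With 100 per arm this happens in 12%, 2% and 0.2%.

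**The case against.** The strongest reply is that {20a} describes the ANOVA in an ordinary way, by naming its factors. The interaction is routine output, {14} names it explicitly, and the planned report of changes between visits fits it. A reader might infer that the group main effect, averaged over baseline, is meant to decide. The documents do not say so, and these three points argue against it. The 11 to 13% figure and the 2D/3 dilution therefore apply only if someone adopts that reading. Under the likelier one, the inflation is 7 to 9%, so a claim that alpha is more than doubled would not hold.

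Nor is the main effect always the weaker ANOVA term. At rho = 0.3 with a sustained difference it has slightly more power than the interaction, and the protocol gives no correlation. Differing results in step 5 also mean only that one test is significant and the other is not, never that the effects point in opposite directions.

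It can further be said that {20a} ties the words primary outcome to the regression alone, and that a condensed article may leave model detail to an analysis plan. An unstated dependent variable would be excusable on that ground. The tension between two stated sections remains. If regression is primary, the trial was sized on another test. If the ANOVA is primary, the term used for sizing is not named where the analysis is described.

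**Conclusion.** The concern holds as an unresolved choice between stated analyses, and it should be fixed. The wording of {20a} and {14} establishes it without any simulation. Its size rests on assumptions that the protocol does not supply: equal between-visit correlation, unit SD and no dropout. Under these, false positives for one distance are about 7 to 9% with two candidates and 11 to 13% with three. The main effect loses power against the interaction at rho 0.5 and above, but not at about 0.3. Among the three candidates, baseline-adjusted regression had the highest or equal-highest power at rho 0.3 to 0.8, which is the reason for preferring it. The documents do not support saying that the sponsor intends a baseline-diluted test.

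**What to change.** In {20a}, name one deciding analysis. The preferred choice is regression of the follow-up distance, or its change, on arm, with the baseline value of that same distance as covariate. State that the adjustment uses baseline values. The sponsor should also state at which of the already defined 3- and 6-month time points the result is read. That is a substantive choice, because the endpoint as written covers both.

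Label the mixed ANOVA supportive, and say that only its group-by-time interaction, not the group or time main effect, counts as evidence of an arm difference. If the sponsor prefers the ANOVA as the deciding analysis, name the interaction, in line with {14}, and make the regression supportive.

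The cost is a few sentences, settled before the outcome data are analysed, with no new visits or measurements. The sponsor gives up the freedom to claim an arm difference from the ANOVA main effects and, if a single time point is chosen, gives the other a lesser role.

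### The minimal important difference is set at the 95% confidence limits of the trial's own mean change, which cannot define importance, and its relation to the 20 m MCID is left unexplained

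*Protocol article*

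**What the plan says.** Everything at issue stands in one paragraph of the protocol article, under Statistical methods for primary and secondary outcomes {20a}.

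- The step is introduced as a way to find the threshold from trial data: "To determine the minimal clinically important difference (MCID), a change in scores for the primary outcome will be calculated by subtracting the baseline outcome". This is done for the 3-month and 6-month values.
- The rule follows: "The least important difference (MID) for improvement and deterioration will be defined by the upper and lower limits of the 95% confidence interval". That interval is the one around mean change in maximal (MWD), pain-free (PFWD) and functional (FWD) walking distance, and a literature citation is given.
- The next sentence reads: "Twenty meters was defined as MCID", citing an earlier study. No distance, test or time point is attached to the 20 m.
- The paragraph then notes that published effects vary. Mean change (SD) in MWD "ranges from 24 (166) to 402 (391) m", and "PFWD changes range from 21 (81) to 182 (249) m".

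The paragraph does not say whether the mean change is pooled over arms or taken per arm, or which of the two follow-up times it uses. It names no external anchor, such as a patient's own rating of change. The abbreviation list has separate entries for MID and MCID but does not relate them.

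**The concern.** A minimal important difference should say how large a change must be to matter. The confidence limits of a mean change answer a different question: how well the mean is known. They are centred on whatever mean the trial observes, they widen with the SD, and they narrow as n grows. A threshold built this way is taken from the result it is meant to judge.

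Two consequences follow from the rule as written, if the upper limit belongs to improvement and the lower to deterioration, as the word order suggests. First, the threshold moves with enrolment even when patients respond identically. Second, once the mean gain is clearly above zero, the deterioration limit is itself a gain.

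The 20 m in the next sentence does not have these faults. But the step before it is presented as the way to determine the MCID, so a reader cannot tell which threshold will be used to interpret the primary outcome. Two thresholds with no stated order also leave room to choose between them after the data are seen.

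**Working it through.** **The article's own figure.** The 20 m is a cited constant with no derivation in the article, so it cannot be reproduced. What can be checked is what the confidence-limit rule yields.

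**Inputs.** Mean change and SD are the extremes quoted in section 20a: MWD 24 (166) and 402 (391) m; PFWD 21 (81) and 182 (249) m. No FWD figures are given. The values of n are:
- 57, one arm at the calculated size (Sample size {14});
- 300, the whole recruitment target pooled (Recruitment {15});
- 100, one arm of those 300, assuming equal allocation.

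No dropout is applied. The means and SDs are published values, used here only to illustrate.

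**Formula.** Limits = mean ± t(0.975, n-1) × SD/√n.

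**Worked cases.**
- MWD 24 (166), n=57: 166/√57 = 21.99; × 2.003 = 44.0; limits -20.0 and 68.0 m.
- MWD 24 (166), n=300: 166/√300 = 9.58; × 1.968 = 18.9; limits 5.1 and 42.9 m.
- MWD 402 (391), n=57: 391/√57 = 51.79; × 2.003 = 103.7; limits 298.3 and 505.7 m.

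**All cases (m).**

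| Mean change (SD) | n=57 | n=100 | n=300 |
|---|---|---|---|
| MWD 24 (166) | -20.0 to 68.0 | -8.9 to 56.9 | 5.1 to 42.9 |
| MWD 402 (391) | 298.3 to 505.7 | 324.4 to 479.6 | 357.6 to 446.4 |
| PFWD 21 (81) | -0.5 to 42.5 | 4.9 to 37.1 | 11.8 to 30.2 |
| PFWD 182 (249) | 115.9 to 248.1 | 132.6 to 231.4 | 153.7 to 210.3 |

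**Reading the table.**
- In the first row, going from n=57 to n=300 lowers the improvement limit by 68.0 - 42.9 = 25.1 m. It raises the deterioration limit by the same amount, from a loss of 20.0 m to a gain of 5.1 m. Only n has changed. As n grows further, both limits close in on the observed mean.
- In the second and fourth rows, the deterioration limit is a gain of more than 100 m at every n.
- At n=57 the improvement limit ranges from 42.5 to 505.7 m, always above 20 m. The two thresholds in the paragraph are therefore not interchangeable.

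**The case against.** Several points count in the plan's favour.

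- **No decision rests on the threshold.** The sample size uses an effect size of 0.25. The primary analysis is regression and a mixed ANOVA, with mean differences and 95% confidence intervals. No success criterion, stopping rule or responder endpoint uses the MID. A reader might infer that the trial's conclusion depends on it; the article does not support that. This point stands and limits the seriousness.
- **The 20 m does not depend on the trial's data.** A reader might infer that every statement of clinical importance would be circular. That goes too far, because the same paragraph offers a benchmark taken from an earlier study. Nor does the article say that individual patients will be classed as improved or deteriorated; section 18a says the change will be a continuous variable.
- **The two thresholds may be meant to coexist.** The 20 m could be an external benchmark, and the MID a trial-based estimate beside it. A flat contradiction is therefore more than the text proves. It is still true that the data-based step is introduced as the way to determine the MCID and that the relation is not explained.
- **The cited method may be anchor-based.** It cannot be checked here, and a journal article condenses. But the article does more than omit a detail: it states a rule, and the rule as stated fails.
- **The limits do not reflect sample size alone.** They also depend on the observed mean and SD. That is correct, but none of the three measures importance to patients.

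**Conclusion.** The point holds as a fault in how the primary outcome will be interpreted. Followed as written, the rule gives a threshold fixed by the observed mean, SD and n. With the article's smallest MWD change, the threshold pair shifts from -20.0 and 68.0 m to 5.1 and 42.9 m between n=57 and n=300. With its largest, the deterioration limit at n=57 is a gain of 298.3 m. The hypothesis tests, the planned estimates and the sample size are unaffected.

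The conclusion rests on three readings: that no anchor is used, since none is stated; that the upper and lower limits belong to improvement and deterioration in that order; and that the published means and SDs indicate the likely scale. The exact metres depend on the last reading and on whether the mean is pooled or per arm. The failure of the rule to measure importance does not.

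**What to change.** In section 20a:

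1. Delete the sentence that defines the MID by confidence limits. If the cited method is anchor-based, replace the sentence with one that names the anchor and the subgroup of patients in whom the change is averaged.
2. Make the pre-specified 20 m the benchmark for interpretation, and state which distance (MWD, PFWD or FWD) and which test (treadmill or 6-minute walk) it applies to.
3. State that the between-arm differences and 95% confidence intervals already planned will be read against that benchmark. Confidence intervals then serve only to show precision.

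Responder proportions are not needed. If change had mean 0 and SD 166 m and were normal (an assumption), 20/166 = 0.12 SD, so about 45% of patients would exceed +20 m and about 45% would fall below -20 m. Such counts would be mostly noise.

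The cost is one sentence removed or rewritten and one or two added, plus a decision by the investigators on where the 20 m applies. That decision should be recorded before outcome data are analysed. No patients, visits or measurements are added.

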#### Behavioral process variables

Process variables are those that can influence and explain initial and behavioral change over time. These psychological variables will play an important role in the change process as initial predictors in explaining the onset of behavioral change and as mediators and/or moderators in explaining the maintenance of change.

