## Dissemination plans {31a}

The WalkingPad program results dissemination plan includes (1) writing and publishing articles in indexed journals, including the WalkingPad protocol and the article on the effectiveness of the intervention program and the set of variables that contribute to adherence to physical exercise in the long term; (2) present the results of the study to health professionals at scientific conferences and events; (3) disseminate the study results to the participants through a social event organized at the end of the study; (4) share the results with the public and other relevant groups, via the media (TV and newspapers) and social networks (Facebook, Instagram, and Twitter); (5) update the WalkingPad project website with pertinent information [5]; systematize guidelines on m-health interventions to increase the effectiveness of HBET programs not only in PAD but also in cardiovascular disease in general.

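### The protocol says SEM will test causal relationships, but for paths from the non-randomised process variables to walking or adherence it tests only conditional association under an assumed model

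*Protocol article*

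**What the plan says.** In the protocol article, Statistical methods for primary and secondary outcomes {20a}, the explanatory analyses come after the primary and secondary outcome analyses. Two purposes are given, in different words:

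- Mediation and moderation: "Mediation and moderation analyses will be performed to examine mechanisms of influence (process variables".
- SEM: "Structural Equation Modeling (SEM) that will allow the analyses of complex relationships between variables and test causal relationships explaining initial behavioral change throughout time".

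The causal wording belongs to SEM. The same section adds, for all tests, "Statistical significance will be set at *P* ≤ 0.05".

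Under Outcomes {12}, Behavioral process variables, the psychological measures are to act "as initial predictors in explaining the onset of behavioral change and as mediators and/or moderators in explaining the maintenance of change". Sequence generation {16a} shows what is randomised: "eligible participants will be randomly assigned to three groups, in blocks of multiples of five, and will be stratified according to" age and baseline MWD. The arm is assigned at random; the process variables are not.

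Dissemination plans {31a} announces an article on the intervention's effectiveness and on "the set of variables that contribute to adherence to physical exercise in the long term".

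**The concern.** A path coefficient in an SEM is tested against zero conditional association, given the arrows and error structure that the analyst has drawn. The direction of the arrows and the absence of shared causes go into the model as assumptions; the test does not examine them. Randomising the arm protects the paths that leave the arm. It does not protect a path from a process variable to walking or adherence, because patients with more favourable scores may differ in other ways that also affect how far or how often they walk. Repeated visits help with order in time but do not remove shared causes.

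At stake is the mechanistic message. If a significant path is read as a tested cause, the planned article could name psychological drivers of adherence that the trial has not shown to be drivers.

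**Working it through.** The protocol gives no figure for this analysis, so there is none to reproduce. The check asks how often a process variable with no effect on the outcome would still give a significant path.

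**Inputs from the document.** Three groups; 57 per group (Sample size {14}); 300 to be recruited (Recruitment {15}), which is 300 / 3 = 100 per group if allocation is equal; two-sided 5% level ({20a}).

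**Assumptions, not in the document.** The arm shifts the process variable M by 0.5 SD in one group. The residual correlation r between M and the outcome Y, caused by one unmodelled shared cause, is 0 to 0.5. There is one process variable and one outcome, with no covariates.

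**Model.** With U the shared cause and e1, e2 independent errors (all standard normal):

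- M = 0.5 × arm + √r × U + √(1 − r) × e1
- Y = √r × U + √(1 − r) × e2

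The true effect of M on Y is zero, and the residual correlation of M and Y is r. The path is tested by regressing Y on the arm indicators and M. The joint test of the indirect effect also requires the arm-to-M path to be significant. There were 4000 replicates per setting.

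**Results (share of trials declared significant).**

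| r | Path, 57 per group | Joint, 57 | Path, 100 per group | Joint, 100 |
|---|---|---|---|---|
| 0 | 4.6% | 3.6% | 4.9% | 4.6% |
| 0.1 | 24% | 19% | 41% | 38% |
| 0.2 | 75% | 57% | 93% | 87% |
| 0.3 | 98% | 75% | 99.95% | 94% |
| 0.5 | 100% | 76% | 100% | 94% |

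**Hand check of the path column.** By Fisher's z, with N patients and two arm indicators partialled out, the test statistic is centred at atanh(r) × √(N − 2 − 3). For N = 3 × 57 = 171, √166 = 12.88.

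- r = 0.1: 0.1003 × 12.88 = 1.29. The rejection rate is about Φ(1.29 − 1.96), or 25%.
- r = 0.2: 0.2027 × 12.88 = 2.61. The rejection rate is about Φ(2.61 − 1.96), or 74%.

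Both agree with the simulation.

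**Hand check of the joint column.** For the arm-to-M path at 57 per group, 0.5 × √(57/2) = 2.67, so power is about Φ(2.67 − 1.96) = 76%. Then 0.76 × 25% = 19% and 0.76 × 74% = 56%, again in agreement. This also explains why the joint test levels off near 76%: the assumed arm effect sets that ceiling.

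Two things follow. With no shared cause the test keeps its nominal level. With one, a larger trial raises the false-positive rate, because the association is real and only its causal reading is false.

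**The case against.** The best defence is that this is one phrase about an explanatory analysis in a condensed article, and that model specification, adjustment sets and sensitivity analyses usually sit in the analysis plan. That stands as far as it goes: the absence of those details is not a fault here. It does not rescue the sentence, because no list of covariates turns a path coefficient into a test of causality.

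Several stronger readings are tempting, and the document does not support them:

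- A reader might infer that the mediation analyses are also presented as causal tests. They are described only as examining mechanisms. The joint-test columns above therefore illustrate the same mechanism and are not evidence about the quoted claim.
- A reader might infer that process variables will be declared causes. No rule says so; they may be reported that way. The wording in Dissemination plans {31a} is one phrase in a publication list and is not a decision rule.
- A reader might infer that the obvious confounders go unmeasured. Table 1 lists depression and anxiety scales at screening, clinical history and medication, a claudication pain scale on the treadmill, and SF-36 mental health and bodily pain. Eligibility criteria {10} exclude several severe comorbidities and any other condition that limits walking. Residual confounding remains possible, but much of the material for adjustment is collected.
- A reader might take the simulated rates as a forecast for this trial. They rest on assumed correlations, an assumed 0.5 SD arm effect and a single-mediator model without covariates, which is much simpler than a longitudinal SEM.

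**Conclusion.** The statement in {20a} is wrong as written for one class of paths: those from non-randomised process variables to walking or adherence. For these, SEM gives conditional association under an assumed model. Paths from the randomised arm to a process variable or to an outcome keep their causal reading. The intention-to-treat arm comparisons, the sample size and the superiority conclusion are untouched.

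The size cannot be fixed from the document. If nothing is shared between process variable and outcome, there is no excess error. If there is a shared cause, even weak residual correlations of 0.1 to 0.2 would take the false-positive rate for a path well above its nominal 5%, and recruiting 300 would increase it further. The point should be corrected because it governs what the explanatory paper may conclude.

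**What to change.** 1. In Statistical methods {20a}, say that SEM assesses whether the data are consistent with a hypothesised causal model, under stated assumptions of no confounding between process variable and outcome.
2. Fix the order: process variable at t2 and outcome at t3, with arm in both equations, adjusted for their t1 values (where one exists; programme adherence has none), age, baseline MWD, and the baseline values of the mood, comorbidity and pain measures already collected. This assumes that the process variables are measured at t2, as Participant timeline {13} suggests; the schedule figure was not available to confirm it.
3. Report the residual correlation between process variable and outcome at which the estimated indirect effect would vanish, so that readers can judge how fragile it is.
4. In Dissemination plans {31a}, write *associated with* in place of *contribute to*.

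Items 1 and 4 are wording and are the essential part. Items 2 and 3 use data already planned and add one sensitivity analysis. The downside is a weaker mechanistic claim.
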